## 4 Background

### 4.1 Palliative chemotherapy in oral cancers

Palliative chemotherapy in head and neck cancers has evolved over three and a half decades. In a small study, use of single agent chemotherapy using cisplatin improved survival over best supportive care. Single agent methotrexate and cisplatin were found to have similar efficacy and were in common use. Use of combination chemotherapy was then tested in subsequent decades. Both 2 drug combinations and 3 drug combinations have been used. However unfortunately none of these combinations provided a survival benefit over single agent platinum therapies with median survival observed to be around 6 - 8 months. However as these combinations provided a higher response rate and longer duration of progression free survival, they were reserved for young, fit and symptomatic patients.

Addition of cetuximab to platinum-based chemotherapy with fluorouracil (platinum–fluorouracil) prolonged the median overall survival from 7.4 months in the chemotherapy-alone group to 10.1 months in the group that received chemotherapy plus cetuximab (hazard ratio for death, 0.80; 95% confidence interval, 0.64 to 0.99;  $P=0.04$ ). Since then several guidelines consider this regimen as the standard of care for palliative chemotherapy regimen in Head and neck cancers. However patients who failed within 1 month of surgery/ radiation or within 6 months of platinum based systemic therapy were excluded in the landmark cetuximab study (EXTREME). These patients were considered as having biologically aggressive disease and a platinum insensitive disease. At present there is no recommended treatment for these patients. In fact the NCCN, ESMO and ICMR guidelines never have addressed these patients separately. There are a few phase 2 studies showing benefit of cetuximab single agent and in combination with chemotherapy in patients progressing on platinum. Hence it can be said that cetuximab may be considered as an sole effective treatment option in this situation.

In developing countries like India access to cetuximab is an issue. In our own experience less than 1% of our patients can afford it. Similar situation prevails in Africa too. In fact as oral cancers are seen in low socioeconomic strata affordability of intravenous chemotherapy is also questionable. Its a sad fact that the maximum benefit of cetuximab was seen in oral cancer patients but oral cancer patients warranting it in low and middle income countries can't afford it. There is a dire need for development of cost effective treatment options in these patients.

## **4.2 Metronomic chemotherapy (celecoxib and oral methotrexate) in Head and Neck cancers**

Metronomic chemotherapy has been developed as a cost effective palliative chemotherapy option in head and neck cancers. Recently we conducted a randomized study of metronomic combination of celecoxib ( 200 mg BD) and oral weekly methotrexate ( 15 mg/m^2 weekly). In this study metronomic chemotherapy was compared against cisplatin chemotherapy. Both the median progression free survival and overall survival were significantly better than cisplatin.. Patients in the metronomic arm had significantly longer PFS (median 101 days, 95% CI: 58.2–143.7 days) compared to the cisplatin arm (median 66 days, 95% CI; 55.8–76.1 days) ( $p = 0.014$ ). The overall survival (OS) was also increased significantly in the metronomic arm (median 249 days, 95% CI: 222.5–275.5 days) compared to the cisplatin arm (median 152 days, 95% CI: 104.2–199.8 days) ( $p = 0.02$ ). This is probably the only trial except EXTREME study ( cetuximab study) which showed a survival benefit of a chemotherapy over cisplatin. As discussed in above section previous studies of combination chemotherapies had failed to show a survival benefit over cisplatin. Additionally these results of metronomic chemotherapy were achieved with much lower side effects and lesser amount of hospital visits. This is an oral chemotherapy regimen and the cost is around 1000-2000 INR per month as opposed to cost of combination chemotherapy ( Paclitaxel+ carboplatin) been around 15,000-20,000 INR month and cost of cetuximab been nearly 4.0 lakh INR / month. Metronomic chemotherapy hence seems an affordable, accessible, safe and efficacious regimen in oral cancers. However the cohort of patients used in our metronomic randomized study had to be either chemonaive or need to have a failure free period of 3 months or more.

In patients who had failed within 1 month of surgery/ radiation or within 6 months of platinum based systemic therapy who couldn't afford cetuximab we offer metronomic chemotherapy at present. In our retrospective experience ( data sent for publication) in oral cancers when such patients with early failures are subjected to metronomic chemotherapy the median survivals are much below expectations. The median estimated overall survival was 110 days (95% CI 85-134 days). There is an urgent unmet need to modify metronomic schedule so that such likely chemoresistant patients can be effectively treated with a cost effective option.

### 4.3 Role of erlotinib in Head and neck cancers

Head and neck cancers have high EGFR expression is seen in around 95% of patients. Oral TKI like erlotinib or gefitinib have shown to have promising activity in head and neck cancers. In a study by Thomas et al in nact setting , erlotinib was given for a median of 20 days. At the time of surgery, tumor shrinkage was observed in nine patients (29%). Even in palliative care setting in our own experience ( data send for publication) second line erlotinib after first line chemotherapy failure provides a median estimated PFS and OS of 110 days (95%CI 61-175 days) and 156 days (95%CI 126-185 days) respectively. Reason for failure to erlotinib is development of resistance. One of the mechanism of resistance to erlotinib is COX-2 mediated angiogenesis.

Celecoxib is an COX-2 inhibitor. Head and neck cancers do have an overexpression of COX-2. Its has been used with erlotinib in chemoprevention studies in Head and neck cancers. In NACT setting too Gross et al studied erlotinib alone and in combination with sulindac (COX inhibitor). Brief treatment with erlotinib significantly decreased proliferation in HNSCC, with additive effect from sulindac. They suggested that efficacy studies of dual EGFR–COX inhibition are justified. Erlotinib in combination with COX-2 has been studied in recurrent head and neck cancers with reradiation. With radiation a dose of erlotinib of 150 mg , a dose of celecoxib up till 400 mg per day was well tolerated. It also lead to promising 1-year locoregional control, progression-free survival, and overall survival rates of 60%, 37%, and 55%, respectively. Combination of erlotinib to the metronomic combination of methotrexate and celecoxib would be an interesting prospect.

### 4.4 Rationale for combination of erlotinib and celecoxib with methotrexate (MTX)

Combination of erlotinib and celecoxib has a strong biological rationale. Metronomic chemotherapy is presumed to act by antiangiogenesis. Hence combination of metronomic with erlotinib would overcome one of the mechanism of resistance of erlotinib. Abcc2, Abcc3, and Abcg2 are multidrug transporters which together mediate the rapid elimination of MTX and 7OH-MTX from the cell. Abcg2 transporter is expressed in head and neck cancer s in around

50-65% of patients. its considered an unfavourable prognostic factor. Erlotinib reverses ABCB1- and ABCG2-mediated MDR in cancer cells through direct inhibition of the drug efflux function of ABCB1 and ABCG2. Hence combination of erlotinib and metronomic chemotherapy is a logical step and may lead to improvement in outcomes.

The use of this regimen on compassionate basis in poor risk head and neck cancers has been described by VP ( author) in his previous institute.( data accepted for publication). In a small prospective study in pretreated patients this combination had a response rate of 46.7% and had a promising median PFS of 148 days (95%CI 95.47-200.52 days). The study met its primary endpoint of improving median PFS over 120 days. Upfront combination of MCT with erlotinib (MCT-E) studied by the author resulted in a 6 month survival of 80%.(accepted for publication). These results need confirmation in a large study, with translational research to identify the mechanism of action, resistance and biomarkers for efficacy prediction.

#### **4.5 Metronomic dose chemosensitivity biological mechanisms: Antiangiogenic**

Angiogenesis is a hallmark of Cancer. Metronomic chemotherapy predominant mechanism of action has been considered as antiangiogenic. The antiangiogenic effect of any chemotherapy modality depends upon the balance it restores between proangiogenic and antiangiogenic factors. Table 1 list details of angiogenic and proangiogenic factors which are implicated in carcinogenesis. In addition it also gives the known effect of metronomic scheduling of chemotherapy on each of these factors and method of measurement. The predominant effect of MCT on angiogenesis is mediated via a decrement in endothelial cells and its progenitors. Decrement in proportion circulating endothelial cells seems to be influenced by the scheduling of chemotherapy dose. Maximum tolerated doses of chemotherapy are associated with a apoptosis of endothelial cells however post this phenomenon a rise in circulating endothelial cells is observed. As opposed to this low dose metronomic scheduling is associated with apoptosis of endothelial cells and it also inhibits mobilization of endothelial progenitor cells. The most biologically effective metronomic dose of a given drug would lead to maximum suppression of circulating endothelial cells.

| Factor                                               | Effect on angiogenesis                       | Known effect of chemotherapy metronomic schedule                                       |
|------------------------------------------------------|----------------------------------------------|----------------------------------------------------------------------------------------|
| Endothelial progenitor cells                         | Pro                                          | Decrement or stable                                                       |
| Serum VEGF                                           | Pro                                          | Decrement or stable                                                       |
| VEGFR 1,2,3                                          | Pro                                          | No effect                                                                 |
| PDGFR-beta                                           | Pro                                          | -                                                                                      |
| Thymidine Phosphorylase                              | Pro                                          | -
( it has been associated with response to metronomic doses of 5 FU)  |
| Tie-2 , Angiopoietin 1-2                             | Anti                                         | -                                                                                      |
| Basic fibroblast growth factor                       | Pro (implicated in resistance)  | -                                                                                      |
| Hypoxia inducible factor 1 alpha                     | Anti                                         | Decrement                                                                 |
| Thrombospondin 1                                     | Anti                                         | Increment in levels                                                   |
| SPARC                                                | Anti                                         | -
(Over expression may be predictive of outcome)                       |
| DLL4 ligand                                          | Pro                                          | -                                                                                      |
| IL-8                                                 | Pro                                          | -                                                                                      |
| Angiostatin,Endostatin,Vasohibin                     | Anti                                         | -                                                                                      |
| CAIX, Plasminogen activator inhibitor-1, Osteopontin | Pro                                          | -                                                                                      |

Table 1 : Pro & antiangiogenic factors

#### 4.6 Metronomic dose chemosensitivity biological mechanisms: Immune system modulation

In addition to having antiangiogenic action metronomic chemotherapy also has anti tumor-immune effects. Metronomic chemotherapy decreases the immunosuppressive effect of

Tumor on host immune system. The major 2 ways by which metronomic chemotherapy helps in restoration of antitumor immune effect are

1. Inhibition of tumor tolerance inducing cells
  - i. Treg (T-regulatory ) cells
  - ii. MDSC (Myeloid derived suppressor cells)
2. Improvement of antitumor response
3. Increased expression of tumor associated antigens
4. Enhancement in dendritic cell functioning

The contribution of these antitumor immune effects of metronomic towards its disease control in lights of its angiogenic properties are not known. FOXP3+Treg cells can be measured in tumor tissue by IHC.

#### **4.7 Need for novel design for finding optimal biological and effective metronomic dose of oral methotrexate**

Metronomic administration is actually a schedule. Same drugs when administered in maximum tolerable dose (MTD) would have different action and the same drugs when administered in 1/10th to 1/3rd of doses of MTD would have different mechanism of action. This phenomenon is seen in multiple chemotherapeutic drugs like paclitaxel, cyclophosphamide, vinca alkaloids and in methotrexate.

The doses selected for metronomic studies have been arbitrary. Doses of 10-33% of MTD have been selected. The dose of methotrexate in Head and neck cancer metronomic was also selected in a similar way. This approach has been criticised by Lam et al. He stressed in his review on having a rationale design for finding an optimal dose of metronomic schedule.

Traditional optimal dose finding designs are based on tolerance to chemotherapy. Doses which lead to acceptable dose limiting toxicities are selected hence these chemotherapy regimes are labelled as maximum tolerable dose (MTD) chemotherapy. The issue in metronomic schedules is that toxicity is not a concern. In our own experience with methotrexate and celecoxib only 18.9% patients had grade 3-4 adverse events (all inclusive) as opposed to 31.4% in cisplatin arm. Not only that toxicity is not a concern but the metronomic effect of a drug is supposed to happen at much lower doses than the MTD hence toxicity as used in traditional dose finding design cannot be used as a parameter for optimal dosing of a metronomic schedule. (Figure 1)

Dose de escalation strategies have been suggested by Emmenegger et al for optimal dosing of antiangiogenic drugs. Figure 1 also clarifies why de escalation may be one of the best methods for optimal dosing of metronomic chemotherapy. As can be seen when the dose level decreases beyond a certain dose level the drug starts to act as an antiangiogenic agent. This property remains upto a certain low dose level and then again it starts disappearing. This window of antiangiogenic property is labelled as antiangiogenic window. This antiangiogenic window was described by Bocci et al and subsequently has been confirmed in other studies. Shaked et al used 4 distinct metronomic chemotherapy regimens in 4 different preclinical tumor models, they established the OBD (optimal biological dose) by determining the maximum efficacy associated with minimum or no toxicity. Subsequently they found each OBD to be strikingly correlating with the maximum reduction in viable peripheral blood circulating vascular endothelial growth factor receptor 2-positive (VEGFR-2+) endothelial precursors (CEPs). Circulating endothelial cell is a surrogate marker for antiangiogenic property of metronomic chemotherapy. The antiangiogenic peak described in figure 1 is associated with maximum inhibition of circulating endothelial cells. Improvement in survival with metronomic schedules and its correlation with CEC/CEPs are described in literature.

[figure not shown]

Figure 1 : As the drug dose decreases the antiangiogenic property of the drug starts increasing at a certain dose level, with further dose de escalation it would further increase however after a certain level of dose de escalation it would then start decreasing. Adapt from Bhattacharjee et al ( unpublished data)

In de escalation strategies the starting dose level is selected on the basis of safety data. The response or endpoint of interest is documented for patients at this starting dose level ( Dose level 0). Subsequently patients are treated at a lower dose level ( Dose level -1). The response or the endpoint of interest is seen and compared to the starting dose level. Depending upon the response the decision is taken whether to continue de escalation or to stop. This design has been used for revealing the optimal dose of bevacizumab. This design is very suitable for

metronomic studies. An modification of this design with bayesian approach and CRM (continuous reassessment model) modelling has been developed and validated by Bhattacharjee et al. (Data sent for publication) It has been validated through data simulation of docetaxel patients where response rate and biomarker was used for decision making. This model takes into account 2 things, disease control (clinical factor) and proportional decline in circulating endothelial cells (biological factor). In the model proposed by Bhattacharjee et al rather than waiting for 3 patients at each dose level, bayesian approach with CRM modelling enables the users to use lesser number of patients and achieve the results early. In this design the efficacy details of each patient are feed into the model and then the model would predict whether the investigators needs to continue at the same dose level or de escalate the doses. The decision rules for the model can be seen in figure 2. This model uses both factors response to MCT and proportional decline in circulating endothelial cells for decision making. Interestingly though response has been used as primary deciding endpoint. In most of the scenarios especially in oral cancers metronomic chemotherapy leads to disease stabilization. In such cases using disease control rate as an criteria for metronomic chemotherapy seems more suitable. Disease control rate is an combination of complete response, partial response and disease stabilization. The variation in CEC measurement is to the tune of 10% or below hence we have used a proportional decline in CEC level of  $> 10\%$  as a deciding factor.

[figure not shown]

Figure 2 : Decision tree.

#### 4.8 PK-PD (Pharmacokinetics- Pharmacodynamics) study of Methotrexate

Pharmacokinetics of methotrexate is well described by two-compartment model. There are many publications describing PK-PD model for methotrexate. one study has described relationship between methotrexate concentration and homocysteine (HCY) levels. An indirect response model was used to describe the HCY concentrations. An  $E_{max}$  model was used to link the PK and PD model (Figure 3).

[figure not shown]

Figure 3. Scheme of the PK/PD model (CL=total body clearance; Q=intercompartmental clearance; V1=volume of the central compartment; V2=volume of the peripheral compartment; HCY=homocysteine;  $k_{in}$ =HCY formation rate constant;  $k_{out}$ =HCY elimination rate constant).

So far, no study is reported to describe PK-PD model for anti-angiogenic effect of methotrexate. Developing a model which describes relationship between methotrexate concentration and CESs and biomarkers like VEGF, sVEGFR-2 and sVEGFR-3 will be helpful to establish the OBD of methotrexate.

## 5 Rationale for the study

In the first stage of the study a metronomic dose of methotrexate would be selected based on both clinical and laboratory endpoints. This would be the first study which would methodically estimate the most optimal biologically effective metronomic dose of a drug.

In the second stage the clinical outcomes of this metronomic regimen would be studied. The mechanism of action, predictors of response and resistance to metronomic chemotherapy would be identified. In addition the pathways which cause resistance would be identified this would open avenue for more research and new drug combinations. Hence this research plan, would tackle an unmet need in oral cancer and would pave way for making a more efficient , accessible and affordable treatment for advanced oral cancers.

## 6 Hypothesis

**Stage 1: Whether a lower dose of methotrexate is clinically and biologically more effective than 15 mg /m^2 weekly dose?** *The dose of methotrexate associated with maximum CBR at 2 months and/or decline in CEC at D7 of first cycle would be selected .*

**Stage 2 : Whether MCT-E combination of celecoxib, erlotinib and methotrexate (in OBD) would lead to a median PFS of > 3 months in platinum insensitive oral cancers?**

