| Feasibility              | We expect to complete accrual for the stage 1 study assuming the maximum number of patients within 24 months. For stage 2 study with maximum accrual in another 24 months.                                                                                                                                                                                                                                                                                                                                                                                                                                                                             |
| Significance             | 
 
1. This would be the first study to systematically determine the optimal biologically and clinically effective metronomic dose of methotrexate
 
2. Evolution in serum and tissue biomarker levels during metronomic chemotherapy and their relationship to disease control would be identified
 
3. Gene expression markers predicting for response would be identified
 
4. Gene expression changes at progression would be identified
 
5. If MCT-E improves median PFS > 3 months then a potential new option would be created in platinum resistant oral cancers
 
 |
| Funding                  | Intramural and Extramural funding to be sought                                                                                                                                                                                                                                                                                                                                                                                                                                                                                                                                                                                                         |

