## 15 Sample size calculation

**Total sample size** : Stage 1 ( 20-30 patients) + Stage 2 ( 76 patients). In stage the continuous reassessment model will be used hence the sample size would be maximum of 30 and minimum around 20. The exact calculations done in both stages are described below in details.

Stage 1 : Flexible-finite sample based approach will be adopted to select the circulating endothelial cells (CEC) interval boundaries and further to use optimum interval design. During the trial, we will continuously update the posterior estimates of decline in CEC and clinical benefit rate and assign patients to the most appropriate dose combination (Figure 1). The Bayesian adaptive screening design will be used to simultaneously select among possible treatment dose combinations. The design is based on formulating the selection procedure as a Bayesian hypothesis testing problem in which the superiority of each treatment combination is equated to a single hypothesis. During the trial conduct, we intend to use the current values of the posterior probabilities of all hypotheses to adaptively allocate patients to treatment combinations. The dose-finding decision will be decided on the twin endpoints the clinical benefit rate at 2 months and proportional decline in CEC at D8 of first cycle. Figure 2 will be used for decision making.

Stage 2: It was assumed that the 3-month progression-free survival (PFS) rate of a standard cancer therapy is 0.50 (H0). An improvement to 0.60 would be considered clinically significant (H1). Assume both the null and alternative PFS distributions follow an exponential distribution. The 1-sided type I error rate of 0.05 and type II error rate of 0.1. Prior assumption includes a fixed enrollment rate of 3 patients per month. We require a stop of 3 months at the end of Stage 1. The library("OptInterim") has been used to calculate the sample size. A 20%extra patient would be taken to account for lost to follow up data. Hence **a total of 76 ( 63 patients +13 patient) sample size is found suitable to carry out the study for stage II with single arm drug therapy.**

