## 16 Outcome measures

### 16.1 Primary outcome :

In stage I the OBD of methotrexate would be identified using response assessment criteria RECIST version 1.1 and flow cytometry measurement of CEC. So a twin primary endpoints of clinical benefit rate at 2 months ( CR or PR or SD persisting till 2 months) and proportional decline in CEC will be used for determination of OBD.

In stage 2 the PFS would be measured in days from date of recruitment in the study till the date of progression (clinical or radiological or both). Median PFS would be estimated by Kaplan Meier survival method.

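### The one stated stage 2 conclusion turns on a median PFS above 3 months, which is the null value, and nothing ties it to the one-sided 0.05 test that sizes the stage

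*Protocol*

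**What the plan says.** Four places in the protocol bear on how stage 2 will be judged.

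- **Section 6 (Hypothesis):** stage 2 asks whether MCT-E at the selected methotrexate dose "would lead to a median PFS of > 3 months in platinum insensitive oral cancers".
- **Section 3 (Concept sheet, Significance row):** if median PFS improves beyond 3 months, "then a potential new option would be created in platinum resistant oral cancers". This is the only place where a stage 2 PFS result leads to a stated conclusion. It comes with no test, confidence bound or error rate.
- **Section 16.1 (Primary outcome):** "Median PFS would be estimated by Kaplan Meier survival method". No test or comparison is named. The primary objective in Section 7.1 is likewise to find the median.
- **Section 15 (Sample size):** "It was assumed that the 3-month progression-free survival (PFS) rate of a standard cancer therapy is 0.50 (H0"), and "An improvement to 0.60 would be considered clinically significant (H1"). The model is "Assume both the null and alternative PFS distributions follow an exponential distribution". The error rates are "The 1-sided type I error rate of 0.05 and type II error rate of 0.1". The size is 63 patients plus 13, giving 76.

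The test in Section 15 does not reappear in the hypothesis, the objectives or the outcome measures.

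**The concern.** The threshold in Sections 3 and 6 is the null value of Section 15. Someone who follows Sections 3 and 16.1 could compute the Kaplan-Meier median, see that it is above 3 months, and report a potential new option. At no step would the one-sided 0.05 test have been used.

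For a regimen sitting exactly at the null, the estimated median falls above or below 3 months about equally often. The error rate in Section 15 would then not apply to the conclusion drawn. In a single-arm trial this comparison with a fixed value is the whole basis of the stage 2 efficacy claim, so the rule that governs it should be explicit.

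**Working it through.** **Inputs.** From Section 15: 3-month PFS S(3) = 0.50 (H0) and 0.60 (H1), exponential PFS, one-sided alpha 0.05, type II error 0.1, accrual 3 per month, 63 patients before and 76 after the addition for losses. Not in the protocol and assumed here: 3 to 12 months of follow-up after the last entry, and no loss to follow-up unless stated.

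**Step 1. Put the hypotheses on one scale.** For an exponential, median = 3 × ln(0.5)/ln S(3).
- H0: S(3) = 0.50 gives 3.00 months.
- H1: S(3) = 0.60 gives 3 × 0.6931/0.5108 = 4.07 months.
- Hazard ratio = ln(0.6)/ln(0.5) = 0.737, and |ln HR| = 0.305.

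A median above 3 months and a 3-month PFS above 0.50 are thus the same hypothesis.

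**Step 2. The plan's own size.** 63 × 1.2 = 75.6, so 76 follows from 63. The 63 itself does not follow from the stated inputs with the tests tried:
- Test of S(3), normal approximation: [(1.645 × 0.5 + 1.282 × 0.490)/0.10]² = about 210 patients (213 by exact binomial).
- Exponential test on the log hazard: [(1.645 + 1.282)/0.305]² = about 92 events.

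The package named in Section 15 was not available to rerun. This is a separate matter, but it explains the power results in Step 5.

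**Step 3. Null pass rate if the observed median is compared with 3 months.** With everyone followed for 3 months, the Kaplan-Meier median exceeds 3 months exactly when more than half the patients are progression-free at 3 months.
- n = 63: P(X ≥ 32), X ~ Bin(63, 0.5) = 0.500.
- n = 76: P(X ≥ 39), X ~ Bin(76, 0.5) = 0.454.

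Simulated Kaplan-Meier medians (4,000 trials each, 3 months of follow-up) gave 0.503 at 63 and 0.460 at 76, and 0.501 at 76 with about 20% loss.

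**Step 4. What a one-sided 0.05 test would need.**
- Exponential median: 3 × exp(1.645/√d) = 3.69 months at d = 63 events and 3.62 at d = 76.
- 3-month PFS, exact binomial: at least 39/63 (alpha 0.038) or 46/76 (alpha 0.042).

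An observed median between 3.0 and about 3.6 months would clear the threshold in Section 3 without rejecting the null of Section 15.

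**Step 5. Power at H1 of the rules that do control the error.**

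| Rule at one-sided 0.05 | n = 63 | n = 76 |
|---|---|---|
| Test of 3-month PFS alone (exact binomial) | 0.43 | 0.51 |
| Exponential log-hazard test, every patient an event: Φ(0.305 × √d − 1.645) | 0.78 | 0.85 |
| One-sample log-rank, simulated, 3 to 12 months of follow-up | 0.74 to 0.78 | 0.81 to 0.84 |

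The log-rank row uses Z = (E − O)/√((E + O)/2), where O is observed events and E is expected events at the null hazard ln(2)/3 per month. It rests on 20,000 simulated trials per setting with uniform entry at 3 per month; the null rejection rate was about 0.05. Using √E as the denominator lowers power slightly, to 0.71 to 0.76 and 0.79 to 0.83. With about 20% loss and 3 months of follow-up, an exponential log-hazard test at n = 76 had power 0.73.

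**The case against.** The strongest reply is that nothing conflicts. Section 6 is a question about the true median, and under Section 15's model it is the alternative to Section 15's null on another scale. Section 16.1 says only that the median will be estimated, and the Significance row is hedged. No section says that an observed median above 3 months is enough. The null, alternative, sidedness and alpha are all given, and the test may well be named in an SAP that is not at hand.

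Much of this stands. A reader might infer that the protocol holds two rival definitions of success, or that following it means a 50% false-positive rate. The documents support neither. The 0.45 to 0.50 figures belong to a rule that the text permits but does not state.

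A reader might also point to Section 4.4, which says of an earlier study of this combination, "The study met its primary endpoint of improving median PFS over 120 days", on a median of 148 days with a 95% interval of 95.47 to 200.52 days. The interval contains 120, so this can look like a precedent for judging by the point estimate. That study's decision rule and error rate are not in the protocol, so it shows nothing about how stage 2 will be judged.

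What the reply does not remove is that the protocol itself fixes a primary analysis and a conclusion, and neither carries the error rate on which it sizes the stage. A test named only in an SAP would leave the Significance row as it is.

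**Conclusion.** The point holds as a gap between the sizing test, the primary analysis and the conclusion. It is not a contradiction between hypotheses. The 3-month threshold is the null value, and the named analysis is estimation only. Were the threshold applied to the observed median, a null regimen would pass with probability 0.500 at 63 patients or 0.454 at 76, against the stated 0.05.

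Those two figures are exact for complete 3-month follow-up and need only S(3) = 0.50. The critical medians of about 3.6 to 3.7 months and the log-rank power also need the exponential model and, for power, the assumed follow-up. The matter is one of specification, cheap to settle, and should be settled before stage 2 results are known so that the rule is credible.

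**What to change.** State one success rule, in the same words, in the Significance row of Section 3, in Section 6 and in Section 16.1. The preferred rule is the one-sample log-rank test of PFS against the exponential null with median 3 months, at one-sided 0.05. It uses all the follow-up and matches the model in Section 15. Report the Kaplan-Meier median and the 3-month PFS with confidence intervals as estimates, not as the pass mark. State the variance form of the test and the minimum follow-up after the last entry.

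The wording change is small, but its cost in power should be stated openly. At H1 the log-rank rule has power of about 0.74 to 0.78 with 63 patients, or 0.81 to 0.84 with 76 and no losses. A rule on 3-month PFS alone would have only 0.43 or 0.51, so a regimen truly at 0.60 would fail about half the time. Neither delivers the 90% in Section 15. Whichever test is chosen, restate the power for that test, or revise the sample size.
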